#### Secondary and exploratory analyses

Secondary and exploratory analyses will investigate the impact of the treatment on other clinically relevant factors, such as implicit processes associated with smoking, alongside examining potential moderators or mediators, such as both global and smoking-related self-efficacy, both global motivation to change and specific motivation to quit smoking, and attitudes towards online interventions. All secondary variables will be assessed at all measurement points (baseline, post, follow-up1 and 2), with the exception of attitudes towards online interventions, which will only be assessed at baseline.

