##### Implicit processes

Changes in implicit processes associated with smoking over time are operationalized as follows:Mean score changes in the nicotine-related approach biases as assessed with the Approach-Avoidance Task [53] adapted for smoking [42].

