### Primary outcome measures measuring implicit processes

Approach biases towards smoking-related stimuli and non-smoking control stimuli are measured using the standard joystick AAT [53] as modified by Machulska et al. [42]. In this task, participants view various images on a computer screen, each slightly tilted either 3° to the left or to the right. Using a Logitech Extreme 3D joystick connected to the computer, participants are instructed to push images rotated to the right and pull images rotated to the left using the joystick. This action causes the images to either shrink or grow in size, depending on the direction of the arm movement. According to Rinck and Becker [53], an approach bias score for a particular picture category (e.g., smoking or control images) is determined by the difference in reaction times (measured in milliseconds, ms) between approach and avoidance movements. Approach biases are calculated for each of the picture categories and across each diagnostic session. A positive difference score indicates that the participant was quicker to approach than to avoid a particular stimulus category, signifying an approach bias. The task includes 50 smoke-related pictures and 50 non-smoking control pictures. Each picture will be presented once in push-away format and once in pull-closer format, respectively, resulting in 200 total trials.

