## Statistical methods

### Statistical methods for primary and secondary outcomes {20a}

Treatment effects on the continuous primary outcomes (i.e., tobacco dependence, smoking intensity, mental health symptoms) will be tested by computing mixed 2 (condition) × 4 (time) analyses of variance (ANOVAs) for repeated measurements for each applied outcome variable. To reduce the likelihood of Type I errors due to multiple comparisons, the false discovery rate (FDR) will be controlled using the Benjamini-Hochberg procedure [7] across the primary outcome measures. In the case of potential violations of the sphericity assumption, the Greenhouse–Geisser method will be applied.

It will be examined whether the experimental condition leads to higher abstinence rates at post- and follow-up assessments using chi-squared tests.

Secondary and exploratory analyses testing for potential mediating variables will be conducted using regression analyses or structural equation modeling. Treatment effects on the AAT will be tested by computing mixed 2 (condition) × 4 (picture category) analyses of variance.

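### The planned AAT analysis names a four-level picture factor that the task does not have and contains no time term, so it does not test change in approach bias

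*Protocol article*

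**What the plan says.** In the protocol article, section {20a}, the paragraph on secondary and exploratory analyses fixes the AAT test: "Treatment effects on the AAT will be tested by computing mixed 2 (condition) × 4 (picture category) analyses of variance". The same section gives the continuous primary outcomes a different model, 2 (condition) × 4 (time).

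The task is described in the data collection part, under the heading "Primary outcome measures measuring implicit processes":

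- Stimuli: "Approach biases towards smoking-related stimuli and non-smoking control stimuli are measured using the standard joystick AAT [53".
- Number of pictures: "The task includes 50 smoke-related pictures and 50 non-smoking control pictures".
- Presentation: "Each picture will be presented once in push-away format and once in pull-closer format, respectively, resulting in 200 total trials".
- Scoring: the bias score is the reaction-time difference between approach and avoidance movements, and "Approach biases are calculated for each of the picture categories and across each diagnostic session".

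The endpoint is defined under Implicit processes: "Mean score changes in the nicotine-related approach biases as assessed with the Approach-Avoidance Task [53] adapted for smoking [42". The timing is set under Secondary and exploratory analyses: "All secondary variables will be assessed at all measurement points (baseline, post, follow-up1 and 2". The only exception there is the questionnaire on attitudes to online interventions, which is given at baseline alone.

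**The concern.** The model in {20a} disagrees with the task and with the endpoint in two ways. First, it has four levels of picture category where the task has two. Second, it has no factor for time and no baseline term, although the outcome is change across four assessments.

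The introduction says the AAT is included to see how implicit biases change in response to cessation treatment. A model without time or baseline does not address that. Nor can the model be fitted as written to the data described, because no four-level picture factor exists. The analyst would have to choose a substitute, possibly after seeing results. The article states this model outright, so the point is an internal contradiction and not a detail left to a later analysis plan.

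**Working it through.** **Inputs, all from the protocol article**

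- Picture categories: 2, with 50 pictures each (AAT description).
- Presentations per picture: 2, one push and one pull (AAT description).
- Stated total: 200 trials (AAT description).
- Assessments: 4, namely t0, t1, t2 and t3 (Outcomes {12}; Secondary and exploratory analyses).
- Conditions: 2; planned sample size 62 (Sample size {14}).

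**Step 1. Reproduce the stated trial count.**

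Trials = categories × pictures per category × presentations per picture = 2 × 50 × 2 = 200. This matches the article.

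**Step 2. Try four categories.**

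- Four categories of 50 pictures: 4 × 50 × 2 = 400 trials, not 200.
- Four categories within 200 trials: 200 / (4 × 2) = 25 pictures each, not 50.

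Neither fits the description.

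**Step 3. Try a charitable reading of the four levels.**

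Two categories × two movement directions give four cells. But direction is not a picture category, and it is already used up in forming the bias score. After scoring, each participant has one value per category per session, that is 2 values at each of 4 sessions. This reading would also still leave out time. The only AAT factor with four levels in the article is time.

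**Step 4. Compare the models (N = 62, complete data, sphericity assumed).**

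| Model | Term | Numerator df | Error df | Uses time? |
|---|---|---|---|---|
| As written, 2 × 4 (picture category) | condition × category | (2−1)(4−1) = 3 | (62−2)(4−1) = 180 | no |
| As written, with the real two categories, 2 × 2 | condition × category | (2−1)(2−1) = 1 | (62−2)(2−1) = 60 | no |
| 2 (condition) × 2 (category) × 4 (time) | three-way interaction | (2−1)(2−1)(4−1) = 3 | (62−2)(2−1)(4−1) = 180 | yes |
| 2 (condition) × 4 (time) on smoking-minus-control score | condition × time | (2−1)(4−1) = 3 | (62−2)(4−1) = 180 | yes |

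The last two rows are the same test. With only two picture categories, the three-way interaction is the condition × time interaction of the difference between them.

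**Step 5. Set the model against the endpoint.**

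A treatment effect on change in bias means that the difference between arms in bias at t1 to t3 departs from that at t0. This is carried by an interaction that includes time, or by a baseline-adjusted contrast. The stated model contains neither.

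**The case against.** The strongest reply is that {20a} speaks of analyses in the plural and that bias is calculated for each diagnostic session. The ANOVA could therefore be meant to be run once per visit. On that reading, the condition × category interaction at t1, t2 or t3 compares randomised arms on smoking versus control bias, which is a valid test of a treatment effect at that visit. This part stands: a reader might infer that the effect on approach bias goes wholly untested, and that would be too strong. But the article does not confirm the per-visit reading. Even on that reading, the comparison would not use baseline, would not test the change that defines the endpoint, and would still carry the wrong number of categories.

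A second reply is that this is probably a drafting slip, in which a two-level picture factor and a four-level time factor were merged. That is likely, but the sentence is the only test the article states for this outcome.

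A reader might also infer, from the heading that calls the AAT a primary measure, that it belongs to the family controlled by the Benjamini-Hochberg procedure and so alters the thresholds for the primary outcomes. The documents do not support this. The Abstract treats implicit biases as secondary. Outcomes {12} and the two lists of primary outcomes do not include the AAT. Section {20a} names the continuous primary outcomes without it and takes it up only in the paragraph on secondary and exploratory analyses. The heading is a stray label. The article also never states a family size, so no threshold can be calculated from it.

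**Conclusion.** The contradiction holds. The stated model has four picture categories where the task has two, a count confirmed by the stated 200 trials, and it omits the four assessments over which the endpoint is defined. As written, it cannot test change in approach bias; at best it compares the arms visit by visit without baseline.

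The reach is limited. The AAT is a secondary outcome, and the smoking and mental health primary models and the sample size are unaffected. The conclusion concerns model specification and does not depend on alpha, power or effect size. The degrees of freedom shown assume 62 participants with complete data and sphericity. No claim is made about the Benjamini-Hochberg family. The correction should be made, but the primary conclusions of the trial do not depend on it.

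**What to change.** Replace the AAT sentence in {20a} with one of these, chosen before the outcome data are examined:

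1. A 2 (condition) × 2 (picture category) × 4 (time, t0 to t3) mixed ANOVA, with the three-way interaction as the test. Equivalently, a 2 (condition) × 4 (time) mixed ANOVA on the smoking-minus-control bias score, with the condition × time interaction as the test.
2. If baseline adjustment is preferred, model t1 to t3 only, with the t0 bias as covariate. Here t0 must not also be a level of time, since the outcome at t0 would then be its own covariate. This model is not equivalent to option 1, so the plan should say which is used and which term is the test.

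The article computes bias separately for each category and does not itself define a smoking-minus-control score. If that score is used, its definition should be added. Separately, relabel the heading of the AAT description as secondary, which is an editorial correction.

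The cost is a change of wording, with no new data, participants or procedures. Trial status gives April 2027 as the end of data collection, and section {25} provides the route for amendments and the registry update.

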### Interim analyses {21b}

No interim analyses or formal stopping rules are planned for this study. The decision is based on the low-risk nature of the intervention, which involves behavioral support without invasive procedures or pharmacological treatments. Additionally, given the naturalistic design, we decided not to conduct interim analyses as they might compromise the integrity of the final data analysis. However, we remain attentive to participant safety and feedback. If any adverse events are reported or significant concerns are raised during participant evaluations (as part of Patient and Public Involvement), appropriate steps, including potential study termination, will be considered and documented accordingly.

### Methods for additional analyses (e.g., subgroup analyses) {20b}

Exploratory and demographic variables will be explored for potential associations with the group condition. If deemed appropriate, analyses regarding treatment effects on primary and secondary outcomes will be re-evaluated to control for potential confounding effects.

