### Sample size {14}

To estimate the required sample size, an a priori power analysis was conducted using G*Power 3.1.9.7 [21]. The primary hypothesis will be tested using a 2 × 4 mixed-design repeated-measures ANOVA (with a power of 1 − *β* = 0.80 and a significance level of *α* = 0.05. This requires a sample size of approximately 62 participants in total, 31 per condition, to detect a moderate effect. No additional participants will be recruited to compensate for potential dropout; instead, the study design follows the intention-to-treat (ITT) principle and employs multiple imputation methods to address missing data. The decision to target a moderate effect size is driven by practical considerations to detect treatment effects that are both statistically significant and practically meaningful.

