## Assignment of interventions: allocation

### Sequence generation {16a}

Participants will undergo random allocation to either the experimental or control condition at a 1:1 ratio. Given the study design, participant or therapist blinding post-allocation is not feasible.

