One significant factor to consider is how motivational variables may influence participant engagement and outcomes. In our psychotherapeutic care research, we opted not to restrict participation based on the willingness to quit smoking. Instead, while participants are required to show an interest in changing their smoking behavior, we proactively invited patients to participate in the study. By evaluating participants across various motivational stages using the transtheoretical model of change [51], we aim to assess the impact of these factors on our primary outcomes. This approach allows us to engage a more diverse and representative sample, rather than relying solely on patients’ initial explicit motivation to quit. This will enable us to examine the effects of actively addressing smoking behavior through interventions on smoking behavior, dependence severity, and mental health symptoms. Secondary analyses of motivation and self-efficacy will be performed to detect confounding effects on the primary outcome, but also to explore possible mechanisms of action which might hold significance for future studies, such as ensuring sufficient self-efficacy before the first session. By examining these factors, we can better understand the underlying processes influencing the effectiveness of the intervention and provide valuable insights for optimizing future research and practice.

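### Supplementary re-analyses of the treatment effects take their covariates from observed association with randomised group, which is chance imbalance and not prognostic value, and the variables are not limited to baseline values

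*Protocol article*

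**What the plan says.** Methods for additional analyses {20b} consists of two sentences. The first reads "Exploratory and demographic variables will be explored for potential associations with the group condition". The second reads "If deemed appropriate, analyses regarding treatment effects on primary and secondary outcomes will be re-evaluated to control for potential confounding effects". No covariate is named, and nothing in the section asks whether a variable predicts the outcome.

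The Discussion adds: "Secondary analyses of motivation and self-efficacy will be performed to detect confounding effects on the primary outcome".

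Other parts of the article that bear on this:

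- **Allocation.** Sequence generation {16a}: "Participants will undergo random allocation to either the experimental or control condition at a 1:1 ratio". Participant timeline {13} puts randomisation after the baseline session. Who will be blinded {17a} says that blinding is not possible.
- **Main analysis.** Statistical methods {20a} fixes a 2 × 4 mixed ANOVA for each continuous primary outcome, with Benjamini-Hochberg control across the primary outcomes.
- **Timing and role of the exploratory variables.** Under Outcomes {12}, all secondary variables except attitudes to online interventions are measured at all four visits. Self-efficacy and motivation are named there as possible moderators or mediators, and self-efficacy also as a secondary outcome.
- **Covariates named in advance.** The choice-of-comparators section {6b} enters dummy variables for additional treatments in the ANOVAs. These treatments are recorded after randomisation.

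**The concern.** Confounding of a randomised comparison by a baseline variable is not something that a test against group can detect. If randomisation worked, every such association is chance. A variable can be imbalanced and irrelevant to the outcome, or balanced and strongly prognostic. The screen picks up the first kind and misses the second. The trial is small ("This requires a sample size of approximately 62 participants in total, 31 per condition, to detect a moderate effect") and has no reserve ("No additional participants will be recruited to compensate for potential dropout"), so forgone precision matters.

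The decision to re-analyse is made after seeing data by arm, by people who know the allocation. The result is an adjusted and an unadjusted version of each treatment effect, with no stated order between them. The false discovery rate control runs across outcomes and not across these versions.

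Motivation and self-efficacy raise a separate problem. After randomisation, a group difference in either may be an effect of the programme. The article treats them as possible mediators in one place and as possible confounders in another, and does not say that only their baseline values may enter as covariates.

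**Working it through.** **1. The plan's own figure.** The sample size section gives 62 patients ("with a power of 1 − *β* = 0.80 and a significance level of *α* = 0.05") without a numerical effect size. With f = 0.25 assumed as moderate, and noncentrality f²(N − k)(m − 1) for k = 2 groups and m = 4 visits, N = 62 gives a power of 0.804 for the condition × time term. The figure is reproduced under those assumptions. The point below does not depend on it, except that the trial is small.

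**2. How often chance alone prompts a re-analysis.** The article gives neither a number of variables nor a threshold, so both are assumed. The lower end of the range is the seven secondary measures listed under Outcomes {12} (approach-avoidance task, GSE, SESS, FEVER, SOC, MTSS, APOI). Demographic variables would add to these. For K independent tests at 5%, P(at least one flagged) = 1 − 0.95^K:

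| K | Probability |
|---|---|
| 7 | 1 − 0.698 = 0.30 |
| 10 | 1 − 0.599 = 0.40 |
| 15 | 1 − 0.463 = 0.54 |

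Several of the scales overlap in content, so independence is an approximation.

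**3. What selection on imbalance does.** Simulation with 20,000 replicates, 31 + 31 patients, one endpoint and eight independent baseline covariates, one of which correlates 0.6 with the outcome. The screen is a t-test at 5%. All these settings are assumptions.

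| Analysis | Type I error | Power at 0.5 SD | Mean SE |
|---|---|---|---|
| Unadjusted | 0.050 | 0.49 | 0.253 |
| Adjusted for whatever is imbalanced | 0.042 | 0.48 | 0.255 |
| Adjusted for the prognostic covariate, named in advance | 0.050 | 0.66 | 0.204 |
| Better of the first two | 0.055 | 0.52 | – |

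The screen added a covariate in 33% to 34% of trials, as expected (1 − 0.95^8 = 0.34). It gained no power and made the test slightly conservative. Choosing the more favourable of two versions raised type I error by about half a percentage point.

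**4. What a pre-named baseline covariate is worth.** Let r be the correlation between baseline and later values, with equal variances. The variance of the group contrast at one visit is then proportional to:

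- post score alone: 1
- change from baseline: 2(1 − r)
- baseline as covariate: 1 − r²

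Against change from baseline the gain is 2(1 − r)/(1 − r²) − 1 = 2/(1 + r) − 1, which is 33% more patients at r = 0.5 and 25% at r = 0.6. Against the post score alone it is 1/(1 − r²) − 1, which is 33% and 56%. The planned ANOVA has baseline as one of its four time levels, so the change comparison is the nearer guide. The power of 0.66 in step 3 belongs to the post-score setting.

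**5. The roles of motivation and self-efficacy, side by side.** Outcomes {12} says that they are measured at every visit and may mediate the effect. The Discussion says that they will be analysed to find confounding. Methods for additional analyses {20b} applies a group-association screen to exploratory variables without naming a visit. At baseline an association with group is chance. At a later visit it may be part of what the trial sets out to estimate.

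**The case against.** The strongest reply is that this is a supplementary analysis. The main model is set out in Statistical methods {20a}, and nothing says that a re-analysis replaces it. That stands. A reader might infer that the primary result itself is open to choice, or that false positives are seriously inflated. The text does not support the first, and the simulation does not support the second.

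A reader might also infer that the plan will adjust for motivation or self-efficacy measured after treatment. The article does not say so. Pairing exploratory with demographic variables fits baseline values, the mediator analyses are assigned to regression or structural equation modelling, and the Discussion's example concerns self-efficacy before the first session. What stands is an ambiguity: no sentence restricts the adjustment to baseline.

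Three further replies have some force:

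- The step from being associated with group to being controlled for is implied by two consecutive sentences. It is a discretionary procedure and not a fixed rule.
- The Discussion does mention effects on the primary outcome, so relation to outcome is not wholly absent. It is simply not made the basis for selection.
- A covariate list can be left to an analysis plan that is not shown. The point here is therefore the method that the article does state, not the missing list.

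Finally, Concealment mechanism {16b} states that there is none, so one could argue that an imbalance need not be chance. That would be a fault in allocation. Screening measured variables would neither establish nor repair it.

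**Conclusion.** The point holds for the supplementary re-analyses and is worth correcting, though it does not undermine the main analysis. Selecting covariates by association with randomised group has no rationale based on outcome, brings no precision, and leaves a discretionary choice of version in an open-label trial. The type I cost is small (about 0.055 against 0.050 in the illustration). The 30% to 54% chance of a spurious flag rests on an assumed 7 to 15 independent tests at 5%.

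The possible precision gain should be quoted as about 25% to 33% more patients at an assumed correlation of 0.6 to 0.5, against a change-from-baseline comparison at one visit. A gain of up to 56% applies only against an unadjusted post-score comparison and should not be claimed for this design. Adjustment for post-randomisation mediators is a risk left open by the wording and not a stated plan.

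**What to change.** In Methods for additional analyses {20b}:

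1. Delete the search for variables associated with group, and show baseline characteristics by arm descriptively.
2. Name one adjusted analysis in advance, with a short set of baseline (t0) covariates used whatever the observed balance: the baseline value of the outcome, baseline FTND, and baseline BDI-II or BSCL. Where the outcome is one of these scales, the set is shorter.
3. Where the baseline outcome is a covariate, take only t1 to t3 as the response, so that the same value does not appear on both sides of the model.
4. Allow only t0 values of motivation and self-efficacy as covariates in treatment-effect analyses. Keep later values in the mediation analyses, and reword the Discussion sentence on confounding to match.
5. Confine the additional-treatment dummies from the comparators section {6b} to a sensitivity analysis, because they are recorded after randomisation and conflict with a baseline-only rule.

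No new data are needed, and data collection runs to April 2027, so there is time. The cost is a few degrees of freedom, a small change of model for the adjusted analysis, and the loss of freedom to choose covariates later.
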